## Abstract

**Background:**

In patients with cirrhosis, the synthesis of coagulation factors can fall short, reflected by a prolonged prothrombin time. Although anticoagulants factors are decreased as well, blood loss during orthotopic liver transplantation can still be excessive. Blood loss during orthotopic liver transplantation is currently managed by transfusion of red blood cell concentrates, platelet concentrates, fresh frozen plasma, and fibrinogen concentrate. Transfusion of these products may paradoxically result in an increased bleeding tendency due to aggravated portal hypertension. The hemostatic effect of these products may therefore be overshadowed by bleeding complications due to volume overload.

In contrast to these transfusion products, prothrombin complex concentrate is a low-volume highly purified concentrate, containing the four vitamin K dependent coagulation factors. Previous studies have suggested that administration of prothrombin complex concentrate is an effective method to normalize a prolonged prothrombin time in patients with liver cirrhosis. We aim to investigate whether the pre-operative administration of prothrombin complex concentrate in patients undergoing liver transplantation for end-stage liver cirrhosis, is a safe and effective method to reduce perioperative blood loss and transfusion requirements.

**Methods/Design:**

This is a double blind, multicenter, placebo-controlled randomized trial.

Cirrhotic patients with a prolonged INR (≥1.5) undergoing liver transplantation will be randomized between placebo or prothrombin complex concentrate administration prior to surgery. Demographic, surgical and transfusion data will be recorded. The primary outcome of this study is RBC transfusion requirements.

**Discussion:**

Patients with advanced cirrhosis have reduced plasma levels of both pro- and anticoagulant coagulation proteins. Prothrombin complex concentrate is a low-volume plasma product that contains both procoagulant and anticoagulant proteins and transfusion will not affect the volume status prior to the surgical procedure. We hypothesize that administration of prothrombin complex concentrate will result in a reduction of perioperative blood loss and transfusion requirements. Theoretically, the administration of prothrombin complex concentrate may be associated with a higher risk of thromboembolic complications. Therefore, thromboembolic complications are an important secondary endpoint and the occurrence of this type of complication will be closely monitored during the study.

**Trial registration:**

The trial is registered at http://www.trialregister.nl with number NTR3174. This registry is accepted by the ICMJE.

## Background

The liver is the site of synthesis of a large part of the proteins involved in the hemostatic system. When the function of the liver is reduced due to acute or chronic liver disease, the hemostatic system can be heavily affected. In patients with cirrhosis, both procoagulant and anticoagulant hemostatic changes have been described, leading to a new rebalanced state [1]. First of all, in the primary hemostasis, platelet number and function can be significantly affected, mostly due to impaired production of thrombopoietin by the liver, reduced platelet survival and increased in platelet consumption [2-4]. The defects in platelet function however, can be compensated by the elevated levels of Von Willebrand factor (VWF), an important endothelial-derived platelet adhesion protein [5,6]. Secondly, there is a decrease in coagulation factors synthesized by the liver. In particular the levels of vitamin K dependent coagulation factors II, VII, IX and X correlate negatively with the severity of disease [7]. However, not only levels of pro-coagulant proteins are decreased in liver disease, the liver also synthesizes coagulation inhibitors and both pro- and anti-fibrinolytic proteins, which are also affected. E.g., plasma levels of vitamin K dependent anti coagulation proteins C and S are decreased [8]. Additionally, in chronic liver disease, a hyperfibrinolytic status has been described [9], although not all studies agree [10]. This hyperfibrinolytic status may be due to decreased plasma levels of antiplasmin and thrombin-activatable fibrinolysis inhibitor, and to a dysbalance in tissue-type plasminogen activator and its inhibitor plasminogen activator inhibitor type 1 [11]. Furthermore, laboratory features of fibrinolysis include increased levels of markers of fibrinolytic activity such as D-dimers, but it must be noted that increased levels of these products may also be caused by accumulation as a result of decreased clearance [10].

Although the defects in coagulation factors would suggest that there is a bleeding tendency, both thrombotic events as well as bleeding complications may occur in patients with advanced liver disease. This might be explained by the fact that, although there is a rebalanced state, both procoagulant and anticoagulant proteins are decreased. The new rebalanced hemostasis is more precarious and susceptible for decompensation towards hypo- or hypercoagulability by factors such as infection, surgery, blood loss, transfusion, hypothermia etc. Furthermore, the bleeding tendency in chronic liver disease patients is much less predictable than in patients with a congenital defect in their coagulation system, e.g. hemophilia [1].

Laboratory tests in chronic liver disease, such as the prothrombin time (PT) and the international normalized ratio (INR), often suggest a hypocoagulable state. However, these tests do not represent the newly formed balance between pro- and anticoagulant proteins, since these tests are not sensitive for deficiencies of the anticoagulant proteins [12]. In contrast with the findings of these routine laboratory tests, the coagulation potential in cirrhotic patients appears to be normal or even superior to that of healthy individuals when tested by thrombin generation assays [13-15].

Orthotopic liver transplantation (OLT) is a major hemostatic challenge, which often requires transfusion of blood products. In the past decades blood loss during OLT has gradually decreased despite the fact that the conventional laboratory measurements like PT and INR still indicate hypocoagulability. It is unclear whether the prolonged PT and INR should be left out of consideration since studies have demonstrated that these measurements do not predict blood loss and transfusion requirements during OLT [16-18]. Furthermore thrombin generation assays during OLT, similar to thrombin generation assays in cirrhotic patients, indicate a normal to hypercoagulable status [19]. Nevertheless, excessive blood loss during OLT does still occur and transfusion of blood products during liver transplantation is associated with a higher risk of mortality, postoperative multi organ dysfunction, and reduced graft survival [20-22].

Clinical strategies to reduce blood loss include the use of blood products to correct pre-existing coagulopathy (assessed by prolonged PT and high INR) by transfusion of fresh frozen plasma (FFP), platelet concentrate, cryoprecipitate or fibrinogen, or antifibrinolytic agents to correct hyperfibrinolysis that may occur during the procedure. A major disadvantage of transfusion of blood products such as FFP is volume overload. To correct a prolonged PT several units of FFP are needed, which will result in an increase in central venous and portal (splanchnic) venous blood pressure, which may in fact increase the bleeding risk. Especially in patients with cirrhosis, who already have a relative fluid overload and increased splanchnic venous circulating volume, intravenous fluid administration will result in an increase in splanchnic venous pressure [23]. Portal and splanchnic hypertension are important risk factors for blood loss during OLT and several authors advocate not correcting pre-operative routine coagulation test by infusion of large volumes of FFP, maintaining a low venous pressure by fluid restriction, or even phlebotomy to prevent excessive blood loss during OLT [24-28].

Prothrombin complex concentrates (PCC) are hemostatically active highly purified concentrates, prepared from pooled plasma [29]. They contain four vitamin K-dependent clotting factors (F) II, VII, IX and X [30]. Previous studies have suggested that administration of PCC is an effective method to normalize a prolonged PT in patients with liver cirrhosis [31-33]. A major advantage of PCC is their low volume load. In contrast to FFP, administration of PCC is not associated with a fluid challenge and the subsequent risk of further increasing portal and systemic venous blood pressure. The question arises whether the administration of a low volume prohemostatic product such as PCC, prior to an invasive procedure in a patient with liver disease, is helpful in reducing blood loss.

PCCs may be related with an increased risk of thromboembolic complications, including venous thromboembolism, acute myocardial infarction, and disseminated intravascular coagulation [34,35]. The link between these reported thromboembolic events and PCC infusion has, however, often been brought into question [30]. Recently, PCC was also proposed for the management of massive peri- and postoperative bleeding [30,36-40]. In some of these reports additional administration of PCC seemed to reduce blood loss and mortality in patients suffering from massive bleeding, either treated with vitamin K antagonists or not. Furthermore, no thromboembolic events were reported. Composition of the currently and previously marketed PCC formulations differs and the thrombotic risk presumably depends on the composition of the product. The thrombotic risk of recently introduced formulations is incompletely evaluated. A review summarizing several aspects of PCC including safety concludes that thromboembolic events are rare and several recent case series have shown that high PCC doses (40 IU/kg) are safe even in high risk patients [41,42].

Cofact® (Sanquin Blood Supply Foundation, The Netherlands) contains balanced amounts of prothrombin complex factors, low levels of activated coagulation factors and a substantial amount of anticoagulant proteins C and S and antithrombin. Both products do not contain heparin. In 1973, Sanquin started with the large-scale production of its first generation of PCC. Since then, no thromboembolic events have been reported. In addition, the manufacturing of this plasma derived product contains 2 robust virus removal steps. The current indication for PCC is bleeding and perioperative prophylaxis of bleeding in acquired or congenital deficiency of (one of) the four vitamin K-dependent clotting factors. This includes the treatment of deficiencies of the four vitamin-K dependant-clotting factors in liver disease.

The ability of PCC to successfully reduce transfusion requirements in liver transplantation has not been established yet. The aim of this trial is to evaluate the hemostatic efficacy and safety of preoperative Cofact® administration (during induction of anaesthesia) on the initial requirement of hemostatic products during surgery in cirrhotic patients with severe coagulopathy undergoing a first liver transplantation.

## Methods/design

### Design and objectives

The study is designed as a multicenter, double blind, randomized placebo-controlled trial. The study is investigator-initiated.

The primary objective is to study the hemostatic efficacy of preoperative PCC administration in patients with cirrhosis and severe coagulopathy undergoing liver transplantation. The hemostatic efficacy will be primarily monitored by recording the need for RBC transfusion.

The secondary objective is to study the hemostatic safety of preoperative PCC administration in patients with cirrhosis undergoing liver transplantation. The hemostatic safety will be monitored by adverse event surveillance and laboratory measurements, with a special focus on thrombogenicity.

All study procedures during this study are summarized in Table 1.

**Table 1 T1:** Timing of study procedures

**Parameters**				**Timepoints**													
	**SEH**	**Surgical procedure**					**Postoperative days**										
		**Anesthesia**	**30 minutes after intervention**	**Pre-anhepatic phase**	**Anhepatic phase**	**Reperfusion phase**	**0/1**	**2**	**3**	**4**	**5**	**6**	**7**	**11**	**14**	**30**	
12-leads ECG	x	According to local protocol							x				x			
Lab	x						x	x	x	x	x	x	x		x	x
Troponin	x						x									
Plasma sample	x	x	**x**	**1 hour after intervention**	**15 minutes after start phase**	**15 minutes after start phase**	x		x		x			x		
				**2 hours after intervention**		**end of surgery**										
Viral safety	x															
TEG/ROTEM					**15 minutes after start phase**	**30 minutes after start phase**										
Blinded INR			**x**				x		x				x			
Ultrasound hepatic vessels		According to local protocol									first 24 h after surgery					
Registration transfusion products			**x**	**x**	**x**	**x**			x				x			
Physical examination with focus on thrombotic and ischemic events																

### Investigational medicinal product (IMP)

The study drug is PCC (Cofact®, Sanquin, The Netherlands) and the placebo is NaCl 0.9%. The known and potential risks of PCC are described in the summary of product characteristics (SPC). In this population, the theoretical risk for thromboembolic complications is a special point of care.

### Endpoints

The primary endpoint will be the number of RBC units transfused during the OLT procedure and in the 24 hour post-surgery period, starting from arrival at the ICU. Other efficacy endpoints are (measured during surgery and during the 24-hour period post-surgery):

• The number of transfused units of fresh-frozen plasma

• The number of transfused units of platelet concentrate

• Fibrinogen concentrate administration

• Estimated blood loss

• Antifibrinolytic drugs

• Crystalloids or colloids administered

• Other escape medication used

• Estimated ascites loss

Safety is a secondary endpoint, safety parameters recorded are:

• All (Serious) Adverse Events with special focus on thromboembolic events

• General and liver-specific laboratory parameters

• Lowest pH, Ca++, lactate, temperature (during and within the first 24 h after surgery)

• Troponin levels, ECG and hepatic vessel ultrasound results

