### Randomization and blinding

The surgical and anesthesiological team must remain blinded for the intervention during the entire duration of the trial. Randomization will be performed using an randomization website. We will stratify per center, and for patient age and gender. Randomization and preparation of the Investigational Medical Product (IMP), whether this is PCC or placebo, will be performed by an independent employee who is not involved in this trial, in the OLT or in post-operative care. The IMP will be delivered in a blinded syringe to the anaesthesiologist and administered by the anaesthesiologist.

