### Transfusion guidelines

The following guidelines have been established for homogenous transfusion policy in all participating centers:

• Fresh frozen plasma: During surgery the use of fresh frozen plasma is allowed in

• case of ongoing bleeding and hypocoagulability indicated by TEG or ROTEM as evaluated by the responsible anesthesiologist. Type of FFP, number of units and volume will be recorded in the case record form (CRF).

• RBC transfusions when hematocrit <25%: Adjustment can be performed at several time points; the units given before surgery do not count for the endpoint calculations, only those given during and directly after surgery (within 24 h of arrival at ICU) count for determination of endpoint. Number of units and volume of transfusion will be recorded in the CRF.

• Phlebotomy when hematocrit >30%: If the hematocrit post-operatively remains

• persistently elevated above 30, a phlebotomy will be performed to lower the hematocrit if the patient is stable and does not have an active bleeding.

• Platelet concentrate: Administration is permitted when platelet counts fall below 50,000/mm^3^ and in the presence o^f^ ongoing blood loss or if it is found necessary e.g. to prevent bleeding during OLT. Type, units and volume of platelet concentrate will be recorded in the CRF.

• Fibrinogen concentrate: Administration is permitted when fibrinogen levels are < 1.0

• g/L in the presence of ongoing blood loss. = > Transfuse 30 mg/kg.

• Tranexamic acid: During the procedure TEG of ROTEM will be used to evaluate fibrinolytic potential during the procedure (see chapter 7.1.3). Upon detection of hyperfibrinolysis on the TEG or ROTEM device in presence of ongoing bleeding due to presumed coagulopathy, a bolus of 1 gram tranexamic acid will be given. The bolus can be repeated in case of insufficient effect on TEG/ROTEM and clinical picture.

• Other transfusion products will be given according to the standard procedures at the individual liver transplantation centers.

• Topical hemostatic agents: Whenever clinically indicated topical administration of hemostatic drugs/agents (e.g. collagen) is allowed (recorded as concomitant medication).

• Cell savers: During the course of this trial, no cell savers will be used by participating patients.

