### Ethical considerations

This trial will be conducted according to the principles of the Declaration of Helsinki and according to Good Clinical Practice (GCP) guidelines. The trial has been approved by the Medical Ethical Committee (MEC) of the University Medical Center Groningen (UMCG) for all Dutch participating centers. The trial has to be approved by the MEC of participating centers in other countries before those centers can start with the inclusions. Prior to randomization, written informed consent has to be obtained from all participants.

All participating centers have an insurance policy for patients participating in this trial in their centers, according to the legal requirements in their country and all centers are required to inform the participating patients about the insurance policy.

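### The FFP and platelet endpoints are raw unit counts although product type and volume are recorded; if unit content differs between centres, the pooled rank test may lose power

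*Protocol article*

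**What the plan says.** All references are to the protocol article.

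- **Endpoints.** Two of the other efficacy endpoints, counted during surgery and the following 24 hours, are "The number of transfused units of fresh-frozen plasma" and "The number of transfused units of platelet concentrate". No size of a unit and no conversion is given there or elsewhere.
- **Transfusion guidelines.** For platelets: "Type, units and volume of platelet concentrate will be recorded in the CRF". The FFP entry likewise asks for type, units and volume. The red-cell entry asks for units and volume but not type. No endpoint uses the recorded type or volume.
- **Design and objectives; Ethical considerations.** The trial is multicentre, and centres outside the Netherlands are foreseen: "The trial has to be approved by the MEC of participating centers in other countries" before they start.
- **Randomization and blinding.** "We will stratify per center, and for patient age and gender".
- **Statistical analysis.** A Mann–Whitney U test compares transfusion needs between the two groups. No stratification by centre is mentioned.
- **Background.** The rationale for the product rests partly on fluid load: "A major advantage of PCC is their low volume load".

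**The concern.** A count of units measures an amount only if a unit holds about the same amount everywhere. The case record form asks for product type and volume for FFP and platelets, so the authors allowed that products might differ, but the endpoint treats all units as interchangeable. If one centre's unit holds less than another's, two patients given the same amount get different scores, and a rank test over all centres mixes that difference into the comparison of arms.

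Two things would be at stake. One is power for two named efficacy endpoints. The other is interpretation: a saving of so many units has no clear size if the unit varies. The recorded millilitres would also lie closer to the volume argument in the Background than a count does.

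**Working it through.** **The plan's own figure.** The Sample size section concerns red cells only (SD 4 U, difference 2 U).
- N = 16σ²/d² = 16 × 16 / 4 = 64 per arm. The usual two-sample formula gives 63, with power 0.801.
- With 10% loss: 64 / 0.9 = 71.1, so 72; or 64 × 1.1 = 70.4, so 71. The stated 70 is within two patients of either.

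The figure reproduces in substance, and nothing below changes it. The article gives no mean, SD or power for FFP or platelets.

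**Inputs for FFP and platelets.** From the article: 1:1 arms of about this size, centre-stratified randomisation, a two-sided 5% level and a Mann–Whitney test without strata. Everything else is assumed:
- 63 evaluable patients per arm, in two types of centre balanced between arms;
- true amounts negative binomial with mean m and dispersion k;
- one type of centre, with 30% or 50% of patients, records f units for each unit recorded elsewhere for the same amount;
- 2,000 runs per setting.

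**Results.** Each cell gives power on a common scale → power on raw units; the two values are for 30% and 50% of patients in the second type of centre.

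| Control mean, k, reduction | f = 1.5 | f = 2 | f = 5 |
|---|---|---|---|
| 2, 1, 50% | 0.730→0.724; 0.727→0.714 | 0.736→0.710; 0.714→0.692 | 0.717→0.624; 0.741→0.620 |
| 4, 2, 36% | 0.712→0.690; 0.708→0.688 | 0.710→0.670; 0.702→0.655 | 0.704→0.511; 0.724→0.492 |
| 8, 5, 25% | 0.712→0.672; 0.736→0.696 | 0.742→0.648; 0.730→0.604 | 0.730→0.398; 0.738→0.278 |

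Subtracting within cells:
- f = 1.5: smallest 0.730 − 0.724 = 0.006, largest 0.040, so about 1–4 points.
- f = 2: smallest 0.714 − 0.692 = 0.022, largest 0.730 − 0.604 = 0.126, so 2–13 points.
- f = 5: smallest 0.717 − 0.624 = 0.093, largest 0.738 − 0.278 = 0.460, so 9–46 points.
- f = 1: the two analyses are identical, so there is no loss.

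**Why the range is wide.** A patient given none scores zero whatever the unit. The expected share of zeros in the control arm is (k/(k+m))^k: (1/3)^1 = 33%, (2/6)^2 = 11% and (5/13)^5 = 0.8% down the rows. The fewer the zeros, and the smaller the natural spread relative to the mean, the more a unit mismatch disturbs the ranks.

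**Bias or noise.** With no treatment effect (m = 4, k = 2, half the patients in each centre type, 4,000 runs), the raw-unit test rejects in 0.039 of trials at f = 2 and 0.016 at f = 5. It becomes conservative; it does not produce false positives.

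**Centre-stratified alternative.** A van Elteren test on raw units, stratified by centre type, has power of about 0.70–0.74 in every cell, the same as the common scale. Multiplying all scores within a stratum by f leaves the ranks in that stratum unchanged.

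**Sensitivity to the model (64 per arm, half the patients in each centre type unless stated).**
- m = 4, k = 3, 35% reduction: about 80% on a common scale; about 78%, 65% and 53% on raw units at f = 1.5, 3 and 5. With only 20% of patients at the differing centres, about 71% at f = 3.
- m = 1.5, k = 0.8, 53% reduction: losses of about 1, 6 and 9 points at f = 1.5, 3 and 5.
- Effect only on whether any product is given (60% v 36% of patients): loss of at most about 1 point, even at f = 5.

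**The case against.** The strongest objection is that the article never says unit content differs. A reader might infer from the recording of type and volume that it does. That does not follow: volume is recorded for red cells too, and such recording is ordinary data capture. The added request for product type, made only for FFP and platelets, suggests possible variation and no more. This part of the objection stands, and it makes every loss above conditional.

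The size also rests on the inputs. The Transfusion guidelines restrict both products, so many patients may receive none, and then the loss shrinks towards zero. This stands as well, and it is why a range is given. The same values of f were applied to both products, with no basis in the article for either.

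A third objection is that a common scale is detail for an analysis plan, which is not shown. This stands in part. A plan could add a volume analysis or a centre stratum. But the article does not leave the scale open: it states units, so changing it later would alter a stated endpoint and is better done in advance.

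Fourth, a centre-stratified test restores the power without touching the endpoint. That is correct for differences between centres. It would not remove differences between product types used within one centre, and it would not give a saving in units a clear size.

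Finally, the volume argument should not be pressed far. The stated objective is haemostatic efficacy, followed mainly through red-cell need, and portal pressure is not an endpoint.

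**Conclusion.** The point holds in conditional form. Two efficacy endpoints are fixed as raw unit counts although data for a common scale are collected, and the named test pools them without a centre stratum. If unit content differs between centres, power for these endpoints falls by about 1–4 points at 1.5-fold, 2–13 at 2-fold and 9–46 at 5-fold under the main assumptions, and by less where many patients receive no product. If units are equivalent, nothing is lost.

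Two stronger readings are not supported. One is that power is in fact lost: the article gives no unit sizes, so this cannot be said. The other is that the comparison is biased: stratifying randomisation by centre balances unit definitions between the arms, and under no effect the test is conservative.

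The matter is minor. These are not primary endpoints, no power is stated for them, and the red-cell endpoint and its sample size are unaffected. It is worth raising because the change costs almost nothing, does no harm if units are equal and helps if they are not.

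**What to change.** - **FFP:** define the endpoint as total ml transfused over the stated window, from the volume already recorded.
- **Platelets:** choose one common scale before unblinding and derive it from recorded type, units and volume. Millilitres need no conversion. Dose equivalents by product type would need a conversion table, which the article does not contain and which would have to be fixed in advance.
- **Raw units:** keep them for both products as a descriptive table, by centre and arm.
- **If raw units remain the endpoint:** replace the plain Mann–Whitney test for these two products with a van Elteren test stratified by centre, which matches the centre stratum of the randomisation.

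The cost is two lines of endpoint wording, one derived variable per product and slightly less familiar units in the report. No new data are needed, and the primary endpoint does not change.

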### Parameters during surgery

The following data will be recorded for participating patients:

– Donor characteristics

– Recipient characteristics

– Liver transplantation technique (conventional versus piggy-back)

– Use of veno-venous bypass

– Data on timing (cold-ischemia time, warm-ischemia time, duration anhepatic phase etc.)

– Surgical abnormalities and technical difficulties including heavy blood loss due to diffuse oozing or accidental vascular injury

– Ascites upon opening abdomen

– Lowest PH, Ca2+, lactate, temperature (during and within the first 24 hours of surgery)

– Transfusion requirements (during and within the first 24 hours of surgery)

– Medication (during and within the first 24 hours of surgery)

– Colloid/Crystalloid/Albumin/Gelatine infusion (during and within the first 24 hours of surgery)

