A potential side effect of PCC in patients with cirrhosis may be a higher risk of thromboembolic complications. Thromboembolic complications are not infrequent after OLT and when thrombosis occurs in one of the hepatic vessels, this may lead to graft loss. In addition, patients undergoing OLT are at increased risk of developing central venous thromboembolic complications such as intracardiac thrombosis or pulmonary embolism [43]. The PCC we are going to use in our study is commercially available under the product name Cofact®. The efficacy and safety of Cofac® has been evaluated in several clinical studies and so far there has been no indication of an increased risk of tromboembolic events in participating patients [42,44-46]. However, most of these trials have been conducted in patients using vitamin K antagonists. There has been no trial reporting the use of Cofact® in cirrhotic patients. With regards to the nature of the product, the disturbed hemostasis in cirrhotic patients and the hemostatic disturbances caused by the OLT, we decided that thromboembolic complications will be an important secondary and safety endpoint in this trial.

For our primary endpoint we have chosen the number of transfused units of RBC. Blood loss will be registered as well, but should be considered as less stable parameter as blood loss will be mixed with ongoing loss of ascites.

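### Ascites loss is classed as an efficacy endpoint without a hemostatic meaning, and the secondary blood-loss comparison is not adjusted for the ascites mixed into it

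*Protocol article*

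**What the plan says.** The Endpoints section makes red-cell units the primary endpoint: "The primary endpoint will be the number of RBC units transfused during the OLT procedure and in the 24 hour post-surgery period". A second list follows under the words "Other efficacy endpoints are (measured during surgery and during the 24-hour period post-surgery". It contains "Estimated blood loss" and, as a separate last item, "Estimated ascites loss". Neither is defined further, and the article does not say whether blood loss is gross or net of ascites.

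The closing Discussion explains why red-cell units were preferred. Blood loss will be recorded, but "should be considered as less stable parameter as blood loss will be mixed with ongoing loss of ascites". The hypothesis in the abstract nevertheless covers both outcomes: PCC "will result in a reduction of perioperative blood loss and transfusion requirements". The aim in the abstract's Background paragraph also names both.

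The Parameters during surgery section separately records "Ascites upon opening abdomen", without saying whether this is a volume, a grade or a yes/no entry.

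For continuous data, the Statistical analysis section plans a parametric or non-parametric comparison between the groups, depending on the distribution. Its regression models are meant to identify risk factors for bleeding and transfusion, not to estimate the treatment effect on blood loss.

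**The concern.** Two things do not fit together.

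First, the efficacy objective in Design and objectives is hemostatic. Nothing in the article says that PCC should raise or lower ascites loss. The one link made between the two, in the Discussion of dosing, runs the other way: some PCC may be lost into the ascites. A quantity with no stated direction of benefit cannot serve as evidence of efficacy, yet it stands in the same list as plasma, platelets and blood loss.

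Second, the protocol identifies ascites as what blurs blood loss and records ascites at opening, but states no use of that record in the blood-loss comparison. At stake is the precision of one secondary comparison, on an outcome that the hypothesis names, and the clarity of the efficacy list.

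**Working it through.** **1. Is the primary analysis involved?** The inputs in the Sample size section are SD 4 units, a difference of 2 units, about 80% power and 10% loss.

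- Two-sample normal formula at two-sided 5%: 2 × (1.960 + 0.842)² × 4² / 2² = 62.8, so 63 per group; 63 / 0.9 = 70. This matches the stated 70.
- The article's own rule: 16 × 4² / 2² = 64; 64 / 0.9 = 71.1, so 72. This is within rounding distance of 70.

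Blood loss and ascites do not enter either calculation. The sample size and the primary test do not depend on this point.

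**2. Bias or noise?** Write recorded blood loss as B + A, where B is blood and A is the ascites mixed in. If treatment does not change A, randomisation gives A the same distribution in both arms. The expected difference in B + A is then the difference in B. A chance imbalance in A can move the estimate in one trial, but the variance of A is already in the standard error. The test keeps its level, and the cost is precision.

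**3. How much precision?** The article gives no mean or SD for blood loss or ascites, so everything here is assumed. Let A be independent of B, with k times its variance.

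- Information kept = 1 / (1 + k).
- For power, assume a standardised effect of 0.5 on B (borrowed from the red-cell assumption, 2 / 4), no effect on A, and 63 evaluable patients per group. Power = Φ(0.5 / √(1 + k) × √(63 / 2) − 1.960).

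| k (assumed) | Information kept | Power |
|---|---|---|
| 0 | 100% | 80% |
| 0.1 | 91% | 76% |
| 0.25 | 80% | 71% |
| 0.5 | 67% | 63% |
| 1 | 50% | 51% |
| 2 | 33% | 37% |

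The table shows the mechanism. It does not estimate the loss in this trial, because nothing in the article supports any particular k.

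**4. What can adjustment recover?** If ascites at opening explains a fraction f of the variance of A, the residual variance is 1 + k(1 − f). With k = 0.5 and f = 0.5 this is 1.25, which moves from the 0.5 row to the 0.25 row. The value of f is also unknown.

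**5. Which ascites variable?** The Intervention and dosage section has the study drug given at induction, no more than 30 minutes before incision. Ascites found at opening could hardly have been changed by then, so it is a safe covariate. Ascites loss over surgery and the next 24 hours is measured after treatment and estimated from the same mixed fluid. It is not a safe covariate.

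**The case against.** The strongest reply is that the protocol already handles the problem. It states the ascites difficulty openly, uses it as a reason to make red-cell units primary, and records blood loss and ascites loss as separate items over the same period, which is what separating them would require. The article condenses a fuller protocol, and the derivation of blood loss may be set out there. The list also holds fluids and escape medication, so it can be read as a broad recording list. All of this is fair, and it limits the point to a secondary endpoint for which no power is claimed.

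A reader might infer more than the text supports:

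- **That ascites loss will be tested and a chance difference read as efficacy.** The Statistical analysis section names no test of it. Only the classification is on the page.
- **That blood loss will certainly be analysed uncorrected.** The article says that blood loss is mixed with ascites and names only unadjusted tests. It does not say that no correction is made.
- **That any difference in ascites loss between arms must be chance.** Ascites at opening predates any plausible drug effect, but the listed endpoint is loss during and after surgery, once the drug has been given.
- **That the blood-loss result is biased or the trial's main conclusion is at risk.** Steps 1 and 2 show otherwise.
- **That subtracting ascites is the obvious remedy.** If the recorded blood loss already excludes some ascites, subtraction corrects twice, and it always carries in the error of the ascites estimate.

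What the reply does not remove is the stated classification, and the lack of any named adjustment beside an acknowledged source of noise.

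**Conclusion.** The point holds in a limited form and is minor. Ascites loss is labelled an efficacy endpoint although the article gives it no hemostatic interpretation. The blood-loss comparison, secondary but named in the abstract's aim and hypothesis, is planned without adjustment for a source of variation that the protocol itself identifies. The consequence is lost precision on that comparison.

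The conclusion that there is noise but no bias assumes that treatment does not change the ascites mixed into recorded blood loss. The size of the loss is unknown: the figures in the table rest on assumed variance ratios, independence, an assumed effect of 0.5, and all of the ascites variation entering the recorded blood loss.

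**What to change.** - Move ascites loss from the efficacy endpoints to the list under Parameters during surgery.
- State in one sentence whether estimated blood loss is gross or net of ascites, so that all centers record it in the same way.
- Compare blood loss between arms with adjustment for ascites at opening, in whatever form it is recorded: as a covariate if it is a volume or grade, as a stratum if it is yes/no. Use transformed or ranked values if the distribution requires it.
- If recorded blood loss is gross, show blood loss net of estimated ascites as a sensitivity figure beside the uncorrected one. If it is already net, omit this.

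The cost is a change of wording and one covariate. No new data, patients or procedures are needed. Error in the ascites-loss estimate reaches only the sensitivity figure. If ascites at opening turns out to be weakly related to recorded blood loss, the adjustment gains little, but it costs almost nothing.
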